#### IOPI Evaluation

The IOPI objectively measures maximum tongue and lip strength. Tongue strength is assessed by measuring the maximum pressure exerted when a person presses a disposable, standard-sized tongue bulb against the roof of the mouth. Lip strength is assessed by measuring the maximum pressure when the bulb is located between the cheek and closed teeth, and the patient contracts the buccinator muscle without biting the bulb. Reference values have been obtained for a healthy population and are provided by the manufacturer [18].

Tongue strength is measured by obtaining maximal tongue elevation pressures. The patient is instructed to “place this bulb in your mouth on the midline of your tongue and push it against the roof of your mouth as hard as you can.” To maximize standard placement, the examiner demonstrates how to place the bulb along the central groove of the tongue blade. Previous research [18] indicates that maximal measures of tongue strength and endurance are best assessed with an unconstrained jaw; participants will be encouraged to gently rest the incisors on the tubing of the IOPI bulb. Each test lasts 7-10 seconds, and all participants will be given verbal encouragement from the examiner for the entire test. The test will be performed three times by each participant, with a brief rest of about 30 seconds between each test while the examiner records the peak pressure obtained. The highest pressure across the three trials will be used as the maximal isometric pressure instead of the mean pressure, which has been used by other researchers [22]. Given the high correlation between the average and maximal pressure and that both are similarly related to oral-phase swallowing function, the use of maximal pressure is more efficient in a clinical setting because it requires no calculation.

Subsequently, the muscle tone of the genioglossus muscle and the buccinator muscle are evaluated, taking three measurements of each and using the highest value.

#### TDS Evaluation

Finally, the tone of the tongue muscles will be measured with a digital spoon, taking three measurements and using the highest obtained. A digital spoon is a kitchen tool used to estimate the weight of food. To develop the TDS, we used the Soehnle Cooking Star Digital Measuring Spoon with graduation from 0.1 grams to 500 grams (ID ID20005876833). This is a handheld instrument with a spoon that can be found on online shopping platforms, consisting of a handle where the “tare” and “hold” buttons are located. Pressing the “hold” button helps to obtain the highest tared value, equivalent to the IOPI peak pressure. To carry out the measurements, the spoon is inverted and a 1-cm^2^ circular sticker is placed on the back to obtain a marked circumference. To measure tongue strength, the subject holds the spoon by the handle and, with their elbow resting on a flat surface, brings the spoon closer to the tongue with an elbow angle of approximately 30°. The subject must then tare the device by pressing the “hold” key, marking 0.0 grams. The subject then presses on the marked circumference with the tip of their tongue. Once done, with the index finger of the hand that is holding the handle, the subject presses the “hold” button. This test is performed entirely by the subject to avoid movements on the spoon that may interfere with the results [20].

The recordings and the data obtained will also be analyzed by another blinded examiner.

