**Methods:**

Patients meeting set criteria will be sequentially enrolled up to a sample size of 40. Twenty patients who meet the inclusion criteria for controls will also be evaluated. Patients will be examined by a qualified phonoaudiologist who will take biometric measurements and administer the Expanded Protocol of Orofacial Myofunctional Evaluation with Scores (OMES), Friedman Staging System, Epworth Sleepiness Scale, and Pittsburgh Sleep Quality Index questionnaires. Measures of upper airway muscle tone will also be performed using the Iowa Oral Performance Instrument and tongue digital spoon devices. Evaluation will be recorded and reevaluated by a second specialist to determine concordance between observers.

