### Procedures

#### Experimental Design

A myofunctional evaluation of patients diagnosed with OSAHS will be performed in the same week as the polysomnography is performed. During this evaluation, patients will be blindly examined by a speech therapist and their examination will be recorded on video for subsequent evaluation.

The patient will sit 1 meter away from the camera with their feet flat on the floor and their back supported by the backrest. The camera (Sony CCD-TRV138 Handycam camcorder) will be placed on a tripod at face and shoulder height.

Evaluation with the OMES protocol (see Multimedia Appendix 3) will then take place, based on the analysis of the following parameters: (1) appearance/posture; (2) mobility; and (3) functions, including respiration, deglutition, and mastication.

As a result of this evaluation with the already validated protocol, the higher the score, the more normal the patient’s stomatognathic system.

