### Statistical Analysis

The data of the study variables will be collected in a database created for the development of the study. In the statistical analysis, the sample will be described through the distribution of frequencies for the categorical variables, and through measures of central tendency and dispersion such as the mean (SD) and median (IQR) for quantitative variables. The distribution of quantitative variables will be examined using the Kolmogorov-Smirnov test. Bivariate analysis of the association between categorical variables will be carried out using the χ^2^ test or Fisher exact test when necessary. The differences between quantitative variables will be analyzed using the Student *t* test or analysis of variance for two or more samples, respectively, and nonparametric tests (Mann-Whitney or Kruskal-Wallis test) will be used if the variables to be analyzed do not follow the normal distribution. The possible correlations between the OMES protocol evaluation and the IOPI values and TDS will be assessed using the Spearman rank correlation coefficient. The consistency and stability of the intra- and interrater measurements (reliability coefficient) will be determined using the split-half method. The level of statistical significance will be set at *P*<.05.

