## Discussion

### Projected Significance

Although Eckert [24] proposed that one of the phenotypes responsible for initiating sleep apnea is the hypotonic pattern in 2016, studies have yet to be performed to confirm this proposal. It is well known that patients with this phenotype can benefit from treatment with a hypoglossal pacemaker, myotonic medication such as desipramine, and myofunctional therapy. We consider that our study will help to identify certain patients with severe OSAHS according to distinct anthropometric and myofunctional features from those of conventional patients (ie, individuals with obesity or with anatomical issues such as big tonsils). Following our experience using the IOPI [18], we consider that patients with a normal BMI, neck and bell circumference, and anatomy of the upper airway will show no relationship with the position of the tongue or the soft palate. We previously demonstrated that Friedman stage is independent from the tone of the muscle of the genioglossus as measured by the IOPI [18].

The patients’ main anomaly will be determined by their responses to the OMES questionnaire, and with the measures of the upper airway muscles using the IOPI and TDS.

The TDS is a simple, reproducible, and affordable method to measure the muscle tone of the tongue for this patient group. We have pioneered the use of this domestic tool to allow patients to obtain immediate feedback of their success in performing myofunctional therapy exercises. In our opinion, the OMES questionnaire is a suitable tool to make a diagnosis for these patients, but can only be performed by specialized phonoaudiologists and requires considerable time. In most countries, there is a lack of phonoaudiologists and the demand on their time means that consultations are short. We contend that we can provide this information with the assistance of the IOPI and TDS that do not require any special training.

The information provided by these two instruments can be correlated with the information obtained by the OMES. In this case, these two measures are fast, simple, reproducible, and provide objective information to both the patient and examiner.

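### Second-examiner agreement on IOPI and TDS re-reads one stored value and cannot support the claim that the devices are reproducible; the three repeat trials could inform it but are assigned only to a maximum

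*Protocol article*

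**What the plan says.** **Second examiner.** The abstract's Methods paragraph states the purpose: "Evaluation will be recorded and reevaluated by a second specialist to determine concordance between observers". Under Experimental Design, patients are seen by a speech therapist and "their examination will be recorded on video for subsequent evaluation". The TDS Evaluation section closes with "The recordings and the data obtained will also be analyzed by another blinded examiner". Distribution of Hospital Visits has a selection visit and a single assessment visit. No second administration of either device is described.

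**Repeat trials.** For IOPI tongue strength, "The test will be performed three times by each participant, with a brief rest of about 30 seconds between each test", and the examiner notes the peak each time. Then: "The highest pressure across the three trials will be used as the maximal isometric pressure instead of the mean pressure". The genioglossus and buccinator measurements follow the same best-of-three rule. The TDS is operated by the subject alone, again "taking three measurements and using the highest obtained".

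**Reliability analysis.** Statistical Analysis promises a coefficient for "The consistency and stability of the intra- and interrater measurements", obtained by the split-half method. It names neither the instrument nor the repeated values that enter it.

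**Claim.** Projected Significance states "The TDS is a simple, reproducible, and affordable method to measure the muscle tone of the tongue for this patient group" and then describes both devices as reproducible. The Introduction criticises OMES as hard to reproduce and asks for something more objective and reproducible.

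**The concern.** An interrater coefficient is informative when each rater makes a judgement or a measurement of their own. That is true of OMES, where two specialists can score one video differently. It is not true of a pressure or weight shown on a display: both examiners have the same number, and they can differ only through a reading or copying slip.

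The error that matters for the devices is how much the value changes when the same person repeats the effort. The second-examiner comparison contains none of that variation. If a coefficient near 1 for IOPI and TDS were set beside a lower one for OMES, the contrast would look like evidence for the article's main argument for the devices, but it would come from the design. The case-control comparison is not affected. What is at stake is what the study can say about the devices as measurements.

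**Working it through.** The article gives no reliability figure or target, so there is no planned number to reproduce. All reliability values below are assumptions.

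**Inputs from the article.** 60 subjects (40 cases, 20 controls), k = 3 trials per device measure, one assessment visit, analysis value = maximum of three.

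**Step 1: does the second reading respond to device error?** Model trial j of subject i as x_ij = t_i + e_ij, with Var(t) = ρ and Var(e) = 1 − ρ, both normal, so that ρ is the single-trial reliability. The table shows the mean one-way ICC over 2,000 simulated studies of 60 subjects.

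| Assumed ρ | Same maximum read twice | Same, 2% of values miscopied (error SD 1) | Maximum of three from a fresh administration | Three trials, single-trial ICC (95% simulation range) |
|---|---|---|---|---|
| 0.3 | 1.00 | 0.99 | 0.43 | 0.30 (0.13-0.45) |
| 0.5 | 1.00 | 0.99 | 0.64 | 0.49 (0.34-0.64) |
| 0.7 | 1.00 | 0.99 | 0.80 | 0.69 (0.58-0.79) |
| 0.9 | 1.00 | 0.99 | 0.94 | 0.90 (0.85-0.93) |

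The two second-reading columns do not move as ρ goes from 0.3 to 0.9. The three-trial ICC follows ρ. The fresh-administration column also shows that the maximum of three has its own reliability, higher than that of a single trial in this model.

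**Step 2: how precise would the three trials be?** For a one-way ICC, F = (1 + (k − 1)·ICC)/(1 − ICC). The limits are (F_L − 1)/(F_L + k − 1) and (F_U − 1)/(F_U + k − 1), where F_L = F/F₀.₉₇₅(n − 1, n(k − 1)) and F_U = F·F₀.₉₇₅(n(k − 1), n − 1). For n = 60 the two quantiles are 1.533 and 1.586.

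- ICC 0.80: F = 2.6/0.2 = 13; F_L = 8.48, F_U = 20.62; interval 7.48/10.48 to 19.62/22.62 = 0.71 to 0.87.
- ICC 0.70: F = 2.4/0.3 = 8; F_L = 5.22, F_U = 12.69; interval 4.22/7.22 to 11.69/14.69 = 0.58 to 0.80.

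The same formula by group, at ICC 0.80, gives 0.69 to 0.88 for the 40 cases and 0.64 to 0.91 for the 20 controls.

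**Step 3: why group matters.** If cases and controls differ by d (in units of the within-group single-trial SD), pooling adds (2/3)(1/3)d² to the between-subject variance. With an assumed d = 1 this is 0.222, and a within-group ICC of 0.70 becomes (0.70 + 0.222)/(1 + 0.222) = 0.75 without any gain in measurement quality.

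**Step 4: does split-half fill the gap?** Split-half correlates two halves of a set of items or trials. It suits a multi-item score such as OMES. Three trials do not divide into equal halves, and two readings of one number have no halves to compare.

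**The case against.** **The tempting stronger reading.** A reader might infer that reproducibility of the devices is never tested and that the repeat trials are thrown away. The article does not support either. It promises intrarater consistency without confining it to OMES, and for a single-value device the only thing that split-half could divide is the three trials. The IOPI peaks are noted trial by trial, and choosing the maximum for analysis does not delete the others. The database layout is in an appendix that is not shown and may already hold all three values. A reader might also infer that intrarater data for OMES are absent; that is detail which a condensed article may leave out, and it is not pressed here.

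**Other points for the plan.** Reproducibility is not among the listed objectives; the statements about it are in the Discussion, and the authors cite their own earlier work on the devices, which cannot be checked here. Nothing says outright that an interrater coefficient will be published for IOPI or TDS. Trials about 30 seconds apart show repeatability within a session only.

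**What stands.** These points limit the claim but do not remove it. The sentence on the second examiner is in the TDS section and covers the data as well as the recordings, so the devices fall within the comparison as written. No later specification can make a coefficient on one shared reading informative about device error. The article does not say that the trials feed the reliability coefficient, and the method it names suits them poorly.

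**Conclusion.** The point holds in a limited form. As described, interrater agreement for IOPI and TDS would be about 0.99 to 1.00 whether true single-trial reliability were 0.3 or 0.9, so it cannot support the statement that the devices are reproducible. The three trials per subject could support a claim of within-session repeatability with usable precision, but the plan assigns them only to a maximum. Nothing described measures reproducibility across sessions or administrations.

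The near-perfect agreement follows from the design and depends only on both examiners having the same stored value; the 0.99 further assumes a 2% copying-error rate. The confidence intervals rest on assumed ICCs of 0.70 and 0.80 and a normal one-way model. The case-control results and the use of the maximum as the analysis value are not in question. The change is worth making because it alters what the study can conclude about the devices.

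**What to change.** 1. Keep all three values for IOPI tongue, IOPI buccinator and TDS in the database.
2. For each measure report a within-session single-trial ICC with its 95% confidence interval and the standard error of measurement (the square root of the within-subject mean square). Do this by group or adjusted for group, and check for a trend over trials, which would point to learning or fatigue.
3. Keep the maximum as the analysis value, and note that its reliability differs from the single-trial ICC.
4. Restrict second-examiner agreement to OMES, and state in Statistical Analysis which instrument and which repeated values each reliability coefficient uses.
5. Limit the statement in Projected Significance to within-session repeatability.

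The cost is a few data fields and a few lines of analysis, with no new visits or staff. The article reports data for 20% of the sample (0.20 × 60 = 12 subjects), so the remaining 48 can contribute even if single TDS values were not kept for the first 12. The downside is a reliability figure that may be less favourable than second-reader agreement.

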### Distribution of Hospital Visits

#### Selection Visit

A patient diagnosed with OSAHS at a pulmonology laboratory by means of an initial sleep study (with measurement of baseline AHI, nighttime oxygen desaturation index, and the lowest nighttime oxygen saturation figures) will be evaluated with respect to the inclusion and exclusion criteria and then informed about the study. After reading the information and having any doubts resolved, the patient will accept and sign the inform consent form in duplicate, taking one copy home.

#### One-off Visit

The patient will be evaluated by the speech therapist and fill in the sleepiness questionnaires, following which the OMES protocol will be applied and the evaluation will be carried out with the IOPI and the TDS.

### Statistical Analysis

The data of the study variables will be collected in a database created for the development of the study. In the statistical analysis, the sample will be described through the distribution of frequencies for the categorical variables, and through measures of central tendency and dispersion such as the mean (SD) and median (IQR) for quantitative variables. The distribution of quantitative variables will be examined using the Kolmogorov-Smirnov test. Bivariate analysis of the association between categorical variables will be carried out using the χ^2^ test or Fisher exact test when necessary. The differences between quantitative variables will be analyzed using the Student *t* test or analysis of variance for two or more samples, respectively, and nonparametric tests (Mann-Whitney or Kruskal-Wallis test) will be used if the variables to be analyzed do not follow the normal distribution. The possible correlations between the OMES protocol evaluation and the IOPI values and TDS will be assessed using the Spearman rank correlation coefficient. The consistency and stability of the intra- and interrater measurements (reliability coefficient) will be determined using the split-half method. The level of statistical significance will be set at *P*<.05.

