### Inclusion Criteria

For cases, adults (aged 18-75 years) who have received a diagnosis of severe OSAHS (AHI>30) without previous experience of the condition and not undergoing treatment owing to different circumstances, who had not undergone any previous treatment for OSAHS, and signed the informed consent form will be included.

For controls, adults with adequate sleep hygiene, no complaints of snoring or daytime sleepiness, and scoring <7 points on the Epworth Sleepiness Scale will be included.

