### Sample Size and Sampling Procedure

The effectiveness of use of the OMES protocol in the evaluation of patients with moderate to severe apnea-hypopnea syndrome will be evaluated from data previously published in studies using this protocol. Following the literature review, patients will be recruited. The sample size will be 60 subjects (40 in the experimental group and 20 in the control group). The sample size was calculated using the XLSTAT statistical software for Excel.

The variables that we are going to measure in all patients are reflected in the data collection table shown in Multimedia Appendix 1 using SPSS Info software, including age, sex, weight, height, ethnicity, BMI, abdominal circumference (at the level of the navel), neck circumference (using a flexible tape around the most prominent part while the patient is standing with their arms by their sides, head erect, and eyes looking ahead), IOPI measurement of tongue strength and the buccinator muscle, AHI, nighttime oxygen desaturation index, lowest overnight oxygen saturation levels, digital spoon measurement of tongue strength, and OMES protocol.

A series of questionnaires will be applied to both groups: Friedman Staging System, Epworth Sleepiness Scale, and Pittsburgh Sleep Quality Index (see Multimedia Appendix 2). An information sheet and information consent will also be provided and signed by patients.

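### With 40 cases and 20 controls, Student's t holds the stated 5% only if the two SDs are similar, and the planned normality check does not look at spread; Welch's t is a cheap improvement

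*Protocol article*

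**What the plan says.** The Statistical Analysis section sets out a two-step rule. Step one: "The distribution of quantitative variables will be examined using the Kolmogorov-Smirnov test". Step two: "The differences between quantitative variables will be analyzed using the Student *t* test" (or analysis of variance for more groups), while Mann-Whitney or Kruskal-Wallis "will be used if the variables to be analyzed do not follow the normal distribution". The threshold is given as "The level of statistical significance will be set at *P*<.05". No unequal-variance form and no check of spread is mentioned.

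Sample Size and Sampling Procedure fixes the allocation: "The sample size will be 60 subjects (40 in the experimental group and 20 in the control group").

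The article states no SD, SD ratio or hypothesis about spread. Two places bear on it indirectly. Projected Significance describes a view in which "one of the phenotypes responsible for initiating sleep apnea is the hypotonic pattern" and hopes to "identify certain patients with severe OSAHS according to distinct anthropometric and myofunctional features from those of conventional patients". Inclusion Criteria selects controls with "no complaints of snoring or daytime sleepiness, and scoring <7 points on the Epworth Sleepiness Scale".

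The Objectives section lists three case-control comparisons (OMES, IOPI, TDS), all as secondary objectives. The Design section calls the study a pilot.

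**The concern.** Student's t pools the two variances, weighting each by its degrees of freedom. With 40 and 20 subjects the pooled estimate is dominated by the cases, while the uncertainty of the mean difference depends more heavily on the smaller control group. If the spreads are equal this does no harm. If they differ, the standard error is wrong: too large when the larger group is the more variable, too small when the smaller group is. A normality check cannot detect this, because two normal samples with different SDs both pass it.

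At stake are the P values, and any intervals built on the pooled variance, for the three group comparisons. The study would lose power if cases are the more variable group, and would produce too many false positives if controls are.

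**Working it through.** **Inputs.** Groups of 40 and 20 (Sample Size and Sampling Procedure); 5% level (Statistical Analysis), taken as two-sided because sidedness is not stated. The SD ratio r = case SD / control SD is an assumption, run from 0.5 to 2, with the control SD set to 1.

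**Formulae.**
- True variance of the mean difference: V = r²/40 + 1/20.
- Variance that Student's t expects: P = [(39r² + 19)/58] × (1/40 + 1/20).
- The nominal critical value on 58 df is 2.002. The test acts as if it were 2.002/√(V/P).
- The type I error is the two-sided tail beyond that value, on f = (39r² + 19)²/(39r⁴ + 19) degrees of freedom.

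**The plan's own figure first.** At r = 1, V = P = 0.075, f = 58 and the error is 5.0%, as stated.

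**Examples.**
- r = 1.5: V = 0.10625, P = 0.13804, √(V/P) = 0.877, acting critical value 2.282, f = 52.7, error 2.7%.
- r = 0.5: V = 0.05625, P = 0.03718, √(V/P) = 1.230, acting critical value 1.627, f = 38.6, error 11.2%.

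**Simulation of the whole rule.** Normal data with equal means, 40,000 replicates per scenario. The article does not say whether Kolmogorov-Smirnov is corrected for estimated parameters (Lilliefors) or whether it is applied per group or pooled, so all four variants were run. The Student and Mann-Whitney columns show the range over separate runs where there was more than one.

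| r | Student, formula | Student, simulated | Two-step rule | Mann-Whitney | Welch |
|---|---|---|---|---|---|
| 0.5 | 11.2% | 10.8–11.3% | 9.8–11.2% | 8.0–8.7% | 4.9% |
| 0.67 | 8.5% | 8.4–8.7% | 8.3–8.7% | 7.2% | 5.1% |
| 1.0 | 5.0% | 5.0% | 5.0–5.1% | 5.0% | 5.1% |
| 1.1* | 4.3% | 4.3–4.4% | 4.2–4.3% | 4.6% | 5.0% |
| 1.25 | 3.5% | 3.4–3.6% | 3.4–3.6% | 4.1% | 4.9% |
| 1.5 | 2.7% | 2.6–2.8% | 2.7–2.9% | 3.8% | 5.1% |
| 2.0 | 1.8% | 1.7–1.9% | 1.7–2.0% | 3.0–3.3% | 4.9% |

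*Simulated as a mixture: 30% of cases shifted by 1 SD.

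The two-step rule follows Student's t almost exactly. The pre-test neither creates the error nor guards against it.

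**Which direction is plausible.** If a fraction f of cases is shifted by d control SDs, the case SD is √(1 + f(1−f)d²). For 30% shifted by 1 SD this is √1.21 = 1.10; for 30% by 2 SD, √1.84 = 1.36; for 50% by 2 SD, √2 = 1.41. With means set equal, the two-step error at 1.36 to 1.41 is 2.9–3.6%.

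**Power** for a difference of 0.8 control SDs (an assumed effect), approximated by Φ(0.8/√V − critical value):
- r = 1.5: 0.8/0.326 = 2.454. Student: Φ(2.454 − 2.282) = 57%. Welch, with critical value about 2.00: Φ(0.454) = 67%. Simulation gives 57–58% for the two-step rule and 67–68% for Welch.
- r = 2: simulation gives about 36% against 53%.
- r = 1: simulation gives 82.3% (Student) against 81.5% (Welch).

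**The case against.** Several objections have force.

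- **The pre-test is not the culprit.** A reader might infer that choosing the test by Kolmogorov-Smirnov distorts the 5%. It does not: with equal SDs the two-step rule gives 5.0–5.1%. Dropping the pre-test while keeping Student's t would mend nothing.
- **Weak power of Kolmogorov-Smirnov is not established for this plan.** For exponential data at n = 20 and 40, the uncorrected test rejects in about 4% and 23–25% of samples, but the Lilliefors form in 58–59% and 90–91%. The article does not say which is meant. A missed rejection also need not do harm: with exponential data of equal spread in both groups, Student's t has an error of 4.9%.
- **The article does not predict unequal spread.** Projected Significance expects to single out some patients. Wider spread in the cases is an inference from that, and a weak mixture has little effect: with 30% or 50% of cases shifted by 1 SD, power is 16.4% against 17.9%, or 37.6% against 40.2%.
- **Inflated false positives are the less likely direction.** For roughly normal data they require the controls to be more variable, which nothing in the article suggests.
- **A condensed article may leave the form of the t test to an analysis plan.** This stands only in part. The article names Student's t and the switch that replaces it, so the suggestion changes a stated choice and does not ask for missing detail.

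One qualification runs the other way. With skewed (lognormal) data of equal means, the two-step rule rejects in 4.7–8.2% of samples at r = 1.5 and 5.8–13.3% at r = 2, because Mann-Whitney then responds to differences other than the mean. Excess rejections are therefore not confined to more variable controls.

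**Conclusion.** The point holds conditionally. At 40 against 20, the equal-variance t test departs from the stated 5% once the SDs differ materially, and the normality check gives no protection. For normal data the error runs from about 2% at a case/control ratio of 2 to about 11% at 0.5; at 1.1 the departure is negligible. Every ratio is an assumption, since the article gives none.

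If the subgroup idea in Projected Significance is right and the data are roughly normal, the test is conservative and the cost is power, about 10 points at a ratio of 1.5 for a difference of 0.8 control SDs. The documents do not support the stronger readings that the results will be miscalibrated in any event, or that false positives are the main danger.

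Severity is minor to moderate: the study is a self-described pilot and the comparisons are secondary objectives. This is a cheap improvement.

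**What to change.** In Statistical Analysis, replace Student's t with Welch's unequal-variance t test for the case-control comparisons of OMES, IOPI and TDS, and report the mean difference with its 95% CI. Give Mann-Whitney as a sensitivity analysis. Describe distributions within each group, but do not let the Kolmogorov-Smirnov result choose the test.

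The change takes one or two sentences and needs no new data. The Results section reports 20% of the planned sample collected, so the change can still be made before the groups are compared.

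The costs are about 1 point of power if the SDs are equal (81.5% against 82.3%) and, if controls turn out to be the more variable group, lower apparent power, because the inflated false-positive rate is removed. Welch is not a full answer to marked skewness: with lognormal data its error ranged from 4.6% to 6.8%, the highest value being at a ratio of 0.5. That is a reason to keep the sensitivity analysis.

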**Objective:**

This protocol describes a case-control clinical trial aimed at determining the muscular features of patients recently diagnosed with severe OSAHS compared with those of healthy controls.

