## Methods

### Design

We designed a prospective controlled quasiexperimental pilot study on patients with severe OSAHS (Figure 1).

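### Controls are not balanced with cases on age, sex or BMI and the stated group comparisons are unadjusted, so an imbalance in these would bias the OMES, IOPI and TDS differences

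*Protocol article*

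**What the plan says.** The Abstract gives the study objective as "determining the muscular features of patients recently diagnosed with severe OSAHS compared with those of healthy controls". In the Objectives section the comparisons with healthy people on OMES, IOPI and TDS are the three secondary objectives; the main objective is to evaluate muscle function in the patients. The groups are not randomised, and the Design section calls the study a quasiexperimental pilot.

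Under Inclusion Criteria, cases are aged 18-75 with AHI above 30 and no previous treatment; the Abstract adds that they are enrolled sequentially. Controls are "adults with adequate sleep hygiene, no complaints of snoring or daytime sleepiness, and scoring <7 points on the Epworth Sleepiness Scale". No age range is given for them. The shared exclusions do not concern age, sex or BMI, and matching, stratification and restriction on these are mentioned nowhere.

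The Sample Size section lists the variables measured in all patients, "including age, sex, weight, height, ethnicity, BMI, abdominal circumference" and neck circumference among them. It sets the numbers: "The sample size will be 60 subjects (40 in the experimental group and 20 in the control group").

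The Statistical Analysis section covers descriptive summaries, chi-square or Fisher tests, and correlation and reliability. For group differences it states: "The differences between quantitative variables will be analyzed using the Student" t test or ANOVA, with Mann-Whitney or Kruskal-Wallis as the nonparametric alternatives. No regression, analysis of covariance or other adjusted comparison appears. The Limitations section does not mention confounding.

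**The concern.** In a non-randomised comparison, a covariate that differs between the groups and is related to the outcome shifts the group difference even when the disease has no effect. Neither of the usual protections is stated here: balance at selection, or adjustment in analysis.

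The protocol itself gives a reason to expect a BMI gap. Under Projected Significance it describes conventional patients as "individuals with obesity or with anatomical issues such as big tonsils", and obese patients are not excluded from a sequential case series. For age, the criteria allow a gap because only one group has a stated range.

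At stake is whether a difference in tongue or cheek pressure or in OMES score can be read as a muscle pattern belonging to severe OSAHS, or may partly reflect age, sex or body size. The protocol hopes to use such patterns to identify candidates for myofunctional therapy, so the distinction matters for what the results are used for.

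**Working it through.** **1. The plan's own figure.** The total of 60 cannot be reproduced. The protocol says "The sample size was calculated using the XLSTAT statistical software for Excel" but gives no effect size, SD or power. Worked backwards (two-sided 0.05, normal approximation), the standard error of a difference in SD units is √(1/20 + 1/40) = 0.274. The difference detectable with 80% power is (1.960 + 0.842) × 0.274 = 0.767 SD. This is the yardstick for the shifts below.

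**2. Inputs.** From the protocol: 40 cases, 20 controls, significance level 0.05. Assumed: a two-sided test; a covariate gap between groups of δ SD; a within-group correlation ρ between covariate and outcome; a true disease effect of zero. The documents give neither δ nor ρ, so ranges are shown.

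**3. Bias.** With the outcome's within-group SD set to 1, the spurious difference is b = δ × ρ.

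**4. Rejection rate of the planned t test.** The statistic follows a noncentral t distribution with 58 degrees of freedom and noncentrality b / 0.274.

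| Example δ, ρ | b (SD) | b / 0.274 | Significant |
|---|---|---|---|
| none | 0 | 0 | 5.0% |
| 0.5, 0.2 | 0.10 | 0.37 | 6.5% |
| 0.5, 0.3 | 0.15 | 0.55 | 8.4% |
| 1.0, 0.2 | 0.20 | 0.73 | 11.1% |
| 1.0, 0.3 | 0.30 | 1.10 | 19.0% |
| 1.0, 0.4 | 0.40 | 1.46 | 30.1% |
| 1.0, 0.5 | 0.50 | 1.83 | 43.5% |

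Simulation agrees. Two separate runs gave 7.9% and 8.8% for the (0.5, 0.3) case, 18.5% and 18.1% for (1.0, 0.3), and 42.5% and 43.3% for (1.0, 0.5). A shift of 0.30 SD is 0.30 / 0.767 = 39% of the difference the study could detect with 80% power.

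**5. The rank test gives no protection.** In the same simulations (4,000 runs per setting), Mann-Whitney was significant in 16.9% at (1.0, 0.3) and 39.7% at (1.0, 0.5), close to the t test.

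**6. Effect of adjusting.** A linear model on group, age, sex and BMI was significant in 4.3% to 5.6% of runs over gaps of 0.5 to 1.0 SD and correlations of 0.2 to 0.5. The fitted model has the same form as the simulated data, so this is what adjustment achieves when the model is right.

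**7. Price of adjusting.** With a true difference of 0.8 SD and ρ = 0.3, the power of that four-term model was:

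| Gap in both age and BMI | Power |
|---|---|
| 0 | 84% |
| 0.5 SD | 77% |
| 0.8 SD | 72% |
| 1.0 SD | 66% |

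The loss comes from overlap between group and covariates, which inflates the variance of the group coefficient. It is not a matter of the few degrees of freedom used. The simulation also let the proportion of one sex rise in cases as the gap grew.

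**The case against.** **The analysis plan may add adjusted models.** This is a condensed article, no SAP is shown, and covariate sets are often specified there. That has some force for the choice of covariates. It has none for the selection of controls, which is a design matter that the article states. The analysis section also names the tests for group differences, and those tests do not suit groups selected in this way.

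**The aims are descriptive.** The protocol asks whether differences exist, makes the comparisons secondary in its list of objectives, and calls the study a pilot. An unadjusted contrast is a legitimate description of two groups. This stands, and it is why the wording of the conclusions matters. But the Abstract puts the comparison first, and a description is hard to use if the groups may differ in age or sex.

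**A reader might infer that the bias will occur, or that the differences found will be age, sex or BMI effects.** The documents do not support that. They give no gaps and no correlation of age, sex or BMI with IOPI, TDS or OMES. The remark about obesity describes conventional patients, from whom the authors hope to distinguish a subgroup; it says nothing about age or sex.

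**A reader might also infer that the covariates are never analysed.** That too goes beyond the text. The section describes the sample, and its tests can be applied to any recorded variable, so an imbalance could be seen. What is not stated is an outcome comparison that takes account of it.

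**Conclusion.** The point holds as a risk left open by the stated design and tests. Controls are unbalanced by design on age, sex and BMI, and the stated comparisons would pass any relevant imbalance into the OMES, IOPI and TDS differences. The false-positive rate under no disease effect could be little above nominal (6.5% for a 0.1 SD shift) or severe (about 43% for a 0.5 SD shift), with 8-9% and 18-19% at shifts of 0.15 and 0.30 SD. All these figures rest on assumed gaps and correlations, a two-sided test and one confounder acting linearly. Which one applies cannot be known from the documents.

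**What to change.** 1. State the 18-75 age range for controls as well as cases.
2. Frequency-match the controls still to be recruited to the cases on sex and age band. The Results section reports data for 20% of the planned sample (0.20 × 60 = 12 people, split by group not given), so most of the sample can still be balanced.
3. Prespecify a linear model of each outcome on group, age and sex. Add BMI in a separate second model, because it may lie on the causal path and its adjusted difference answers a different question.
4. Report adjusted differences with 95% CIs beside the unadjusted ones, and word the conclusions as differences between groups, not as effects of OSAHS.

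The cost is a slight restriction on which controls can be taken, and some added analysis text; the covariates are already on the data form. Intervals will widen if the groups differ much on the covariates: in the setting worked above, power falls from about 84% with no gap to 77% at 0.5 SD gaps and 66% at 1.0 SD gaps. With only 20 controls, matching during recruitment is therefore worth more than adjustment alone, and the number of covariates should stay small.
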